### Statistical Analyses

Focusing on the *primary* hypothesis, we will conduct an ANCOVA with the 6-month follow-up ANELT scores as dependent variable, with group assignment (anodal-tDCS or sham-tDCS) as independent variable, and baseline ANELT scores as covariate. Further covariates are the stratification parameters specified above (i.e., age, aphasia severity at baseline, and center). The trial outcome will be analyzed on an “intention-to-treat” basis in the total group. In the event of missing values, multiple imputation methods will be applied, if appropriate. Regarding the *secondary* hypotheses, data will be analyzed using standard statistical methods while adjusting for possible confounders, including the stratification parameters. As participants may differentially benefit from anodal-tDCS of M1 depending on type of aphasia, exploratory subgroup analyses will determine response rates related to individual syndromes.

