### Recruitment and Setting

Individuals with chronic post-stroke aphasia will be recruited in more than 18 in- and outpatient rehabilitation centers throughout Germany (for an updated list of study sites, see record on ClinicalTrials.gov; identifier: NCT03930121). A similar network of rehabilitation centers proved to be time- and cost-effective in a previous large-scale RCT with long-term follow-ups (5).

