### Randomization

In addition to intensive SLT, participants will either receive anodal-tDCS or sham-tDCS, depending on group assignment (allocation ratio of 1:1). Groups will be stratified-randomized according to age (<60 vs. ≥ 60 years), aphasia severity at baseline (AAT *t*-score classification at screening: severe vs. mild-to-moderate aphasic symptoms), and center (for details, see Figure 1). Block randomization will be used (randomly varying block sizes of 4 and 6).

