### Sample Size Estimates

We expect a between-group difference on the ANELT of at least three points at the 6-month follow-up. An independent-sample *t*-test with a two-sided significance level of 0.05 has a power of 80% to detect an average between-group difference of 3.0 points (standard deviation: 5.8) at the 6-month follow-up if data from 120 participants are analyzed, according to calculations using nQuery with raw data from previous work (12). Assuming a drop-out rate of 10%, 130 individuals will be recruited. Determining samples sizes with *t*-tests is a conservative approach: the planned analysis of covariance (ANCOVA) with (1–*p*^2^) × *n* participants has the same power as a *t*-test with *n* participants, where *p* is the variance deflation factor, calculated by the correlation of baseline and follow-up measures (30). In the worst case of *p* = 0, the resulting sample size corresponds to a *t*-test.

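### The t-test sample size is not the worst case for the planned ANCOVA: with centre as a fixed effect the floor is about 72–75% power, not 80%

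*Protocol article*

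**What the plan says.** Sample Size Estimates (protocol article) bases the trial on an independent-samples t-test "with a two-sided significance level of 0.05", which "has a power of 80% to detect an average between-group difference of 3.0 points (standard deviation: 5.8") "if data from 120 participants are analyzed". It calls this conservative because the ANCOVA needs only a fraction (1 − p²) of the t-test's participants, where p is derived from the correlation between baseline and follow-up. It closes by saying that in the worst case, p = 0, "the resulting sample size corresponds to a" t-test.

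Statistical Analyses defines that ANCOVA: 6-month ANELT on group and baseline ANELT, and then "Further covariates are the stratification parameters specified above (i.e., age, aphasia severity at baseline, and center").

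Recruitment and Setting gives the number of centres as "more than 18 in- and outpatient rehabilitation centers throughout Germany". Randomization stratifies jointly by age (two levels), severity (two levels) and centre, in blocks of 4 and 6 with 1:1 allocation. The article does not say whether centre is fixed or random, or whether small centres are pooled.

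**The concern.** The (1 − p²) rule compares a t-test with an ANCOVA that has one covariate, the baseline score. It says nothing about the cost of adding a factor with 19 or more levels. A fixed centre effect restricts the treatment comparison to contrasts within centres. Where the arms are unequal within a centre, part of the information is lost, and a centre with only one arm contributes none.

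The randomization does little to prevent this. Nineteen centres × 2 × 2 gives 76 strata, and 130/76 is about 1.7 participants per stratum, so most blocks of 4 or 6 never fill.

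At stake is the guarantee itself. The article offers 80% as the floor whatever the baseline correlation turns out to be, and the model that it plans to fit need not have that floor.

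**Working it through.** **Inputs from the article.** Two-sided alpha 0.05, difference 3.0, SD 5.8, 120 analysed (60 per arm), 130 recruited, 1:1 allocation, blocks of 4 and 6 within age × severity × centre, more than 18 centres.

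**Assumptions.** The article gives neither the exact number of centres nor their sizes. I took 19 to 25 centres, of equal or unequal size. Age and severity were split 50:50, with skewed splits as a check. The 120 analysed were a random subset of the 130. The worst case means zero baseline correlation and zero between-centre variance.

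**Step 1: the plan's own figure.** Noncentrality = 3.0 / (5.8 × √(1/60 + 1/60)) = 2.833. With 118 df, power is 80.2%, so the stated 80% reproduces.

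**Step 2: lost degrees of freedom alone.** With 19 centres the residual df are 120 − (intercept 1 + group 1 + baseline 1 + age 1 + severity 1 + centre 18) = 97. The same noncentrality gives 80.1%, so the loss of df is negligible.

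**Step 3: within-centre imbalance.** The stated randomization was simulated. In each run the treatment indicator was regressed on baseline, age, severity and fixed centre. Its residual sum of squares S sets the variance of the treatment estimate, SD²/S. Perfect balance gives S = 30, so the variance inflation is V = 30/S and the noncentrality becomes about 2.833/√V.

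| Model and centres (120 analysed, zero correlation) | V | Power |
|---|---|---|
| Baseline, age, severity; no centre | 1.03 | 79.2% |
| Plus fixed centre, 19 equal / unequal | 1.146 / 1.138 | 74.7% / 74.9% |
| Plus fixed centre, 22 equal / unequal | 1.184 / 1.166 | 73.2% / 73.8% |
| Plus fixed centre, 24 equal / unequal | – | 72.3% / 73.1% |
| Plus fixed centre, 25 equal / unequal | 1.220 / 1.197 | 71.9% / 72.7% |

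Hand check for 19 equal centres: 2.833/√1.146 = 2.646, which with 97 df gives 74.5%. Skewed age and severity splits with 19 centres give 75.0–75.6%. Nearly all of the loss therefore comes from arm imbalance within small centres.

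**Step 4: break-even.** A baseline correlation r multiplies the residual variance by (1 − r²). The cost of centre is cancelled when (1 − r²) × V = 1. With V = 1.146, r² = 1 − 1/1.146 = 0.127, so r = 0.36. With V = 1.138, r = 0.35. Simulation agrees: power at r = 0.35 is 79.9–80.2%, at 0.5 about 86%, and at 0.6 about 91%. By the same arithmetic, with r = 0, centre would have to explain 12–13% of the variance. With 25 equal centres the break-even rises to r = √(1 − 1/1.22) = 0.42.

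**Step 5: random centre intercept.** With zero between-centre variance, taken as known, the centre term drops out and power is about 79%, as in the first row of the table.

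**The case against.** The article's worst case concerns a single parameter, the baseline correlation, and the sentence can be read as a remark about that parameter alone. The 72–75% also needs three conditions together: fixed centre, no baseline correlation and no between-centre variance. Zero correlation is implausible for the same test given twice to the same people, and under Primary Outcome the article credits the ANELT with high reliability on retesting. How small centres are handled is commonly settled in an analysis plan that is not shown.

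Much of this stands. A reader might infer that the trial's realistic power is 72–75%. The documents do not support that: they give no value for the correlation, and with 19 centres a modest one of about 0.35 is enough to restore 80%. A reader might also infer that several centres will have only one arm. That depends on centre sizes the article does not give: about 0.2–1 such centres if sizes are equal, 3–5 under the unequal sizes assumed here. The power loss is nearly the same in both cases.

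What does not stand is that nothing needs correcting. The sentence refers to the planned ANCOVA, and the article itself chose zero correlation as its guarantee. The next section puts centre into that model, and fixed is the ordinary reading of an ANCOVA covariate. The objection is to a positive statement, not to missing detail.

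**Conclusion.** The statement that the t-test size is the worst case is wrong for the model as described. Under fixed centre effects, zero baseline correlation, zero between-centre variance and 120 analysed, the floor is about 75% with 19 centres and 72–73% with 24, a shortfall of roughly 5 to 8 percentage points from 80.2%. The figures rest on assumed centre numbers and sizes; more centres lower them further. If the full plan specifies a random centre effect, the article's claim is approximately true, at about 79%.

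The point corrects the argument for conservatism. It does not show that the sample size of 130 is too small.

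**What to change.** **Minimum.** Reword the worst-case sentence so that it describes the model to be fitted: about 72–75% power at p = 0 with fixed centre effects, with the baseline correlation at which 80% is regained (about 0.35 with 19 centres). Update this to the actual number of centres. This changes wording only.

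**Preferred.** Before unblinding, specify centre as a random intercept in a linear mixed model with Kenward-Roger degrees of freedom, keeping treatment, baseline ANELT, age and severity as fixed effects. Centre stays in the model, as the stratification calls for, and worst-case power returns to about 79%. The cost is a distributional assumption for the centre effects, which 19 or more centres can support. No participants, visits or procedures change.

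A pre-specified rule for pooling small centres, or fixed centre with the corrected power statement, would also be acceptable.

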*Selected linguistic functions, Aachen Aphasia Test (13); Apraxia of speech, Hierarchical Word Lists (14); Non-verbal working memory, Corsi Block-Tapping Task (15); Communication ability (primary outcome), Amsterdam Nijmegen Everyday Language Test (A-scale; parallel versions used in counterbalanced order across participants) (6); Naming ability, personally relevant trained and untrained items, consistent with previous work (12); (Non-)verbal communication, Communicative-Pragmatic Screening (18), Scenario Test (Nobis-Bosch et al. in preparation), and Communicative Effectiveness Index (20); Attention and executive function, reaction-speed subscales from NeuroCogFX (21); Non-verbal episodic memory, Figure Recognition Task from Benton Visual Retention Test (22); Mood, German version of the 10-item Stroke Aphasic Depression Questionnaire (SADQH-10) (23); Health-related quality of life, SAQOL-39g (24); EQ-5D-5L and EQ-5D-VAS (25); Health economic evaluation: direct and indirect costs during the 12-month study period (determined by the self-developed Patient Resource Consumption Questionnaire and based on common standardized unit cost assumptions), and Quality-Adjusted Life Years (derived from the EQ-5D-5L data) (26); Unpaid support provided by family members or friends, Burden of informal caregivers (27); (Serious) adverse events, tDCS Safety Questionnaire (28); Subjective treatment-induced change, as experienced by patients, therapists, and relatives, Minimal Important Difference (29)*.

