### Primary Outcome

Communication ability in 10 everyday-life situations will be evaluated by parallel versions of the ANELT (A-scale) (6). ANELT has good psychometric properties, including high test-retest reliability and sensitivity to treatment-induced progress in chronic post-stroke aphasia (2, 5). Each testing session will be videotaped and scored offline by the external Endpoint Committee.

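### The ANELT is given in counterbalanced parallel versions, but the primary ANCOVA has no term for version order; adding one is a cheap, optional gain in precision

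*Protocol article*

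**What the plan says.** The Primary Outcome section states that communication ability is "evaluated by parallel versions of the ANELT (A-scale") and scored offline by a blinded committee. The Table 1 footnote adds that these are "parallel versions used in counterbalanced order across participants". Table 1 schedules the ANELT at baseline, post-treatment, 6 months and 12 months. The article does not give the number of versions, which version is used at which visit, or any score difference between versions.

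Under Statistical Analyses, "we will conduct an ANCOVA with the 6-month follow-up ANELT scores as dependent variable", with treatment group and the baseline score in the model. The list then ends: "Further covariates are the stratification parameters specified above (i.e., age, aphasia severity at baseline, and center"). For the secondary hypotheses the wording is looser: possible confounders are adjusted for, and the stratification factors are named as examples.

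The sample size rests on an unadjusted t-test that "has a power of 80% to detect an average between-group difference of 3.0 points", with an SD of 5.8 and 120 participants analysed.

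**The concern.** Version order is fixed by design before treatment, so it can safely be a covariate. Counterbalancing removes a version effect from the average over participants, but not from the spread between them. Unless the model has a version term, what the baseline score does not absorb goes into the residual.

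The baseline covariate can make this worse. If a participant takes the easier version at baseline and the harder one at the endpoint, the outcome is lower and the score predicted from baseline is higher, so the two discrepancies add. If both visits use the same version, they largely cancel. At stake is precision on the primary endpoint, using information that should already be on the test form.

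**Working it through.** **Plan's own figure.** Difference 3.0, SD 5.8, two-sided alpha 0.05 and 60 per arm give an exact t-test power of 80.2%. The stated 80% with 120 analysed is reproduced.

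**Inputs.** From the article: 120 analysed, 1:1 allocation, SD 5.8 (variance 33.64), target 3.0 points. Assumed, because the article is silent: two versions used equally often; a mean version difference D of 0, 1 or 2 points; a baseline/6-month correlation r of 0.5, 0.7 or 0.8; version order independent of arm; SD 5.8 describing the ANELT score at each visit without version variance.

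**Formula.** With version removed, the ANCOVA residual variance is 33.64(1 − r²). With version ignored and the baseline slope taken as r, each order group is displaced from the common line by
- (1 + r)D/2 if baseline and endpoint versions differ,
- (1 − r)D/2 if they are the same.

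The variance ratio, version ignored over version removed, is therefore 1 + [(1 ± r)D/2]² / [33.64(1 − r²)].

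Example, D = 2, r = 0.7, different versions: 1.7² = 2.89; 33.64 × 0.51 = 17.16; ratio 1 + 2.89/17.16 = 1.17.

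| r | D = 1, different | D = 2, different | D = 2, same |
|---|---|---|---|
| 0.5 | 1.02 | 1.09 | 1.01 |
| 0.7 | 1.04 | 1.17 | 1.01 |
| 0.8 | 1.07 | 1.27 | 1.00 |

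**Simulation.** ANCOVA with and without an order term (1,500 trials per setting) gave ratios of 1.01, 1.03 and 1.06 at D = 1 and 1.08, 1.16 and 1.25 at D = 2 for r = 0.5, 0.7 and 0.8 with different versions. It gave 0.99 to 1.01 with the same version and 0.99 at D = 0. These are slightly below the formula because the fitted slope is a little under r when version is ignored, and because the order term itself costs a degree of freedom. The simulated figures are the ones to use: 1-6% and 8-25%.

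**Validity.** In a second simulation (4,000 trials per setting, D = 1 to 3, r = 0 or 0.7), the model without a version term gave estimates averaging close to the true 3.0. Its type I error was between 4.4% and 5.4%.

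**Power, different versions, 60 per arm.**

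| r | version removed | D = 1 ignored | D = 2 ignored |
|---|---|---|---|
| 0 | 80.23% | 79.94% | 79.07% |
| 0.5 | 90.05% | 89.41% | 87.47% |
| 0.7 | 97.58% | 97.09% | 95.35% |
| 0.8 | 99.68% | 99.50% | 98.61% |

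The loss is at most 0.6 percentage points at D = 1 and 2.6 at D = 2. At r = 0, the case on which the trial is sized, it is 0.3 and 1.2. If SD 5.8 already contains version variance, the 80% sizing loses nothing, and at r = 0 removing version raises power to 80.5% (D = 1) or 81.4% (D = 2).

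**The case against.** The strongest reply is that nothing here is wrong. The model fits the randomization and the sizing argument, parallel forms are meant to be equivalent, no version difference is documented, and a test-form term could sit in an analysis plan that is not shown. Most of this stands, and it is why the point is only a refinement. It does not remove the point altogether: the article states the covariates of the primary model as a complete list, so a plan that follows it leaves version order out, and a plan that adds it departs from the published model.

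A reader might infer three stronger things that the documents do not support.

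- *That any version difference weakens the primary comparison.* With two versions in simple alternation over the four visits (A-B-A-B), baseline and 6 months share a version and the gain at the primary endpoint is about nil. It would then fall on the post-treatment and 12-month comparisons. The article does not show which scheme applies.
- *That a chance imbalance of version order between arms is a second problem, a bias or confounding.* It is the same sampling error seen from another side. At r = 0.7 and D = 2 the standard error with version removed is 5.8 × √0.51 × √(4/120) = 0.756. The between-arm difference in order share has SD √(0.25 × 2/60) = 0.091, which shifts the estimate by 0.091 × 1.7 × 2 = 0.31 points. Then 0.31²/0.756² = 0.17, exactly the inflation from the formula above.
- *That counterbalancing shows the versions to be unequal.* The article gives no such reason; it can be an ordinary precaution.

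**Conclusion.** The point holds as an optional precision improvement. The primary covariate list omits a factor that the design itself counterbalances. The cost of the omission depends on two things the article does not report: whether the versions differ in difficulty, and whether baseline and endpoint versions differ within a participant. If both are so, with two versions and a correlation of 0.5 to 0.8, the variance of the treatment effect is about 1-6% larger at D = 1 and 8-25% larger at D = 2. If either is not so, the cost is about nil.

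The larger percentages arise at high correlation, where power is already far above 80%, so they should not be read as a threat to the trial's power. The primary analysis is valid as written.

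**What to change.** Under Statistical Analyses, add ANELT version order (or the version used at baseline and at the endpoint) as a fixed covariate in the 6-month ANCOVA, and use the same term in the post-treatment and 12-month ANELT models. Specify it before unblinding, so that it cannot look data-driven.

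The cost is one line of text and one degree of freedom with two orders, slightly more if there are more orders. If the versions turn out equivalent, the loss is under 1% of variance. No extra participants, visits or tests are needed.

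The allocation list need not change. Balancing order within arms would mean linking test forms to a masked, encrypted sequence with restricted access, and the covariate makes that unnecessary.

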### Safety, Protocol, and Data Monitoring

Safety, protocol, and data monitoring will be conducted by the Clinical Trials Coordination Center of the University Medicine Greifswald. For constant tDCS applied over cortical areas in awake humans, potential minor side effects are skin irritation, initial phosphenes, headache, dizziness, and itching under the electrode. Intensity, duration and frequency of tDCS are within the limits suggested in current guidelines (31). Number and type of adverse events will be diagnosed by a study physician, reported to the Clinical Trial Management within seven days, and classified using a standard questionnaire (28). In addition, serious adverse events will be reported to an independent Data Safety and Monitoring Board that will advise whether to continue, modify or stop the treatment and decide whether to unmask the group assignment. To ensure treatment fidelity and participant compliance, all training sessions will be audiotaped (naming therapy) or documented in written form (communicative-pragmatic therapy). These materials will be continuously evaluated by the Clinical Trial Management. Moreover, the Data Safety and Monitoring Board will participate in annual meetings with the Clinical Trial Management to ensure adherence to the study protocol, including blinding integrity. All primary and secondary outcomes will be scored by the external Endpoint Committee blinded to group assignment and time of assessment. Access to the dataset and stimulator-generated randomization sequence will be restricted to the Clinical Trial Management and the Data Safety and Monitoring Board. To protect individual privacy before, during and after the trial, the dataset will be stored, analyzed and archived in a pseudonymized manner.

## Discussion

The proposed protocol of a phase-III RCT aims to demonstrate that intensive SLT combined with anodal-tDCS benefits verbal communication and parameters related to activities of daily living in chronic post-stroke aphasia. Previous phase-II RCT data have shown that naming therapy combined with anodal-tDCS improves performance of trained items and, to a smaller degree, untrained items alongside proxy-rated communication ability (12, 19). Progress in communication ability may have a positive impact on associated factors, such as severity of post-stroke depression. Thus, the current RCT considers the overall outcome of intensive SLT on measures evaluating linguistic-executive skills, attention, memory, emotional well-being, quality of life, and health economic costs. In- and exclusion criteria are kept liberal to allow generalization of the expected results to realistic routine-healthcare conditions. The age split of 60 years for randomization was chosen to control for age-dependent cerebral changes, such as microangiopathy or reduced neuroplasticity. Covering both utterance-centered and communicative-pragmatic treatment strategies, the selected SLT methods reflect best-practice guidelines in aphasia rehabilitation (5).

There are two major reasons for stimulating M1 instead of individually determined intact perilesional brain regions. *First*, perilesional stimulation requires pre-treatment mapping of preserved language-related neural activity. Such an approach is time-consuming, expensive, and involves technical expertise usually not available outside specialized research centers. *Second*, the rationale for anodal-tDCS of M1 comes from neuroscience evidence suggesting that the motor system is anatomically and functionally linked with perisylvian eloquent areas (32–34). Moreover, behavioral studies revealed that engaging the primary motor cortex facilitates language processing in healthy individuals (35–37) and in persons with aphasia (38–43). Accordingly, phase-II RCT data confirm that anodal-tDCS of M1 leads to elevated naming and communication performance in chronic post-stroke aphasia (12) while increasing activity and connectivity in the preserved language network (19). Although the neural bases of recovery from aphasia are not fully understood, anodal-tDCS of M1 may affect sensorimotor coupling via pathways from posterior language regions (44) or alter connectivity of motor and prefrontal areas relevant to speech (45). Current spread may also change excitability in premotor or prefrontal regions (46) and hence support domain-general cognitive function, resulting in better language performance across different aphasia subtypes, severity levels, and lesion sites (47). To confirm the local influence of anodal-tDCS on M1 and to investigate the underlying neural mechanisms, an add-on study will focus on individualized modeling of current flow in a subset of rehabilitation centers with access to high-resolution MRI.

In conclusion, intensive SLT can relieve symptoms in chronic post-stroke aphasia, but effect sizes are moderate (5). This highlights the need to explore adjunct strategies, such as anodal-tDCS, to enhance training effectiveness. Recently, we provided phase-II RCT data indicating that intensive SLT combined with anodal-tDCS of M1 benefits naming and communication ability in chronic post-stroke aphasia, with medium-to-large effect sizes (12). The present study seeks to establish anodal-tDCS of M1 by substantiating our previous findings in a phase-III RCT with adequate power, ecologically valid outcomes, and evidence-based SLT. After trial completion, a workshop with relevant stakeholders will ensure transfer into best-practice guidelines and successful integration within clinical routine.

